**Methods and analysis:**

To investigate these gaps, a cross-over randomised clinical trial has been embedded within routine clinical care. Seventy-six pregnant women in their first trimester with type 1 or type 2 diabetes (with or without medication) attending their routine antenatal appointments at National Health Service (NHS) Leeds Teaching Hospitals will be recruited. Following informed consent, data on women’s health, glycaemia, pregnancy and delivery will be shared by the NHS with researchers. At each visit in the first (10–12 weeks), second (18–20 weeks) and third (28–34 weeks) trimester, participants will be asked for consent to: (1) lifestyle and diet questionnaires, (2) blood for research purposes and (3) analysis of urine collected at clinical visits. Additionally, participants will be asked to consume two blinded meals in duplicate in second and third trimester. Glycaemia will be assessed by continuous glucose monitoring as part of routine care. The primary outcome is the effect of experimental meals (high vs low protein) on postprandial glycaemia. Secondary outcomes include (1) the association between dysglycaemia and maternal and newborn health, and (2) the association between maternal metabolic profiles in early pregnancy with dysglycaemia in later pregnancy.

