### Sample size using power calculation

CGM data provide numerous metrics to offer unique insight into variations and deviations of glucose levels over time—area under the curve (AUC), mean glucose, coefficient of variation of glucose, mean amplitude of glucose excursions (MAGE) and time in range (TIR).^14^ Additionally, there is no current evidence regarding the effect of diet composition and glycaemic load on metrics of CGM in pregnant women with diabetes throughout the duration of pregnancy. Therefore, we have elected to focus on AUC as the primary metric because it is easily interpretable and commonly used to quantify postprandial glycaemia. Evidence from Fabricatore e*t al*^15^ demonstrated a significant association (p<0.05) between self-reported GI and measures of CGM (including AUC, mean glucose and % time hyperglycaemic) in a clinical trial of 21 women and 5 men with type 2 diabetes. Assuming similar effect sizes between GI (per unit) and AUC glucose (β=0.36 mg/dL/min; R^2^=0.38), mean glucose (β=0.02 mol/L; R^2^=0.38) and time spent >10 mol/L blood glucose (β=0.41%; R^2^=0.36), we will have sufficient power (power=0.90) to detect a significant pairwise effect of GI on these parameters with 63 participants. Another study by Law *et al* suggested that this will provide sufficient power (power=0.90) to compare subgroups of participants (stratified by body mass index (BMI), age, type of diabetes) and test for significant differences (of a minimum effect size) in AUC glucose (±61 mmol/L/min), mean glucose (±0.5 mmol/L) and % time hyperglycaemic (±3.7%).^16^ Finally, given the comparable proportions of women reported to be of white European versus non-white European ancestry (57% vs 43%) or diet versus diet+medication (46% vs 54%), we also anticipate having adequate power to compare these confounders of glycaemic response. To account for attrition, we will increase our recruitment target by 20% above our calculated, suggesting a target sample size of 76 recruited women. We have allocated ~6 months to recruit 76 women (at 10–12 weeks’ gestation) and ~15 months for study completion (ie, final delivery). All power analyses were performed using G*Power (V.3.1).^17^

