### Study participation inclusion and exclusion criteria

All pregnant women over the age of 18 years, with pre-existing T1DM or T2DM, in their first trimester and a singleton pregnancy, will be considered for the study. Women who develop diabetes in pregnancy (i.e., gestational diabetes) will not be eligible for the study because they would not be offered CGM until 26–28 weeks’ gestation. Exclusion criteria include: (1) inability to understand English sufficiently to read the participant information sheet and provide consent (online supplemental materials A–C); (2) mental and/or psychological disorders that undermine informed consent; (3) cancer, digestive tract disorders; (4) lack of internet access on a computer or tablet at home. Detailed exclusion criteria are shown in table 1 (study screening questionnaires are provided in online supplemental materials D and E).

10.1136/bmjopen-2022-065388.supp1Supplementary data

**Table 1 T1:** Study participant inclusion and exclusion criteria

Inclusion criteria	Exclusion criteria
Women aged 18–45 years	Women under 18 or above 45 years of age
Singleton pregnancy	Multiple pregnancy
Women in the first trimester of pregnancy	Fetal congenital abnormality
Previously diagnosed with type 1 or type 2 diabetes mellitus	No diagnosis of diabetes
	Diagnosis of gestational diabetes
	Significant coexistent medical condition (e.g., overt diabetes complications, cancer, gut mobility or digestion disorder)
	Significant psychological (e.g., anorexia, bulimia) and/or mental disorders which undermine informed consent
	Dietary allergies or intolerance for the experimental meals
	Lack of internet access on a computer or tablet at home
	Unable to understand written English and provide informed consent

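### The adequate-power claim for diet versus diet+medication is unsupported: its 46%/54% split is unsourced, needs most type 2 women to be on diet alone, and medication is partly confounded with diabetes type

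*Protocol article*

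**What the plan says.** In the protocol article, the section on sample size ends its power argument with two splits. It reasons that, "given the comparable proportions of women reported to be of white European versus non-white European ancestry (57% vs 43"%) and a second near-even split, "diet versus diet+medication (46% vs 54%), we also anticipate having adequate power to compare these confounders of glycaemic response". No effect size, SD, numeric power or source population is attached to the diet and medication comparison.

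The 63 comes from a different question, the effect of glycaemic index on CGM metrics: "we will have sufficient power (power=0.90) to detect a significant pairwise effect of GI on these parameters with 63 participants". The same section then claims 0.90 power to compare subgroups, including subgroups by type of diabetes.

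On who enters, the abstract describes "Seventy-six pregnant women in their first trimester with type 1 or type 2 diabetes (with or without medication"). The eligibility section requires women "with pre-existing T1DM or T2DM, in their first trimester and a singleton pregnancy" and states: "Women who develop diabetes in pregnancy (i.e., gestational diabetes) will not be eligible for the study". Table 1 repeats this by listing "Diagnosis of gestational diabetes" as an exclusion. The expected mix of type 1 and type 2 is not given.

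**The concern.** The power statement depends entirely on two groups of similar size. Eligibility limits where diet-only women can come from. If every woman with type 1 diabetes uses insulin, the diet-only group is drawn from type 2 women alone, while the medicated group holds all the type 1 women plus the remaining type 2 women. Two things follow.

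- A near-even split requires a large fraction of the type 2 women to be on diet alone, and that fraction rises with the type 1 share.
- A pooled comparison of the two groups is in part a comparison of type 2 with type 1. A difference in AUC glucose could be read as a medication effect when some of it belongs to diabetes type. Separating the two costs power that a near-even headline split does not show.

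At stake is how far readers can rely on this secondary comparison, not the meal comparison.

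**Working it through.** **Inputs from the protocol.** 46% and 54%; 63 evaluable women; power 0.90; 20% inflation; significance at p<0.05 (taken as two-sided).

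**Assumptions, not in the protocol.** All type 1 women use insulin. The type 1 share p is not stated, so a range is shown. No difference or SD is given for this comparison, so a standardised benchmark is used.

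**1. The plan's own figures.** 63 × 1.2 = 75.6, which rounds up to the stated 76. The adequate-power statement itself cannot be reproduced, because it has no effect size. As a benchmark, 46% of 63 is 29, giving 29 vs 34. A two-sample t-test (noncentral t, two-sided 5%) then has 90% power at 0.83 SD and 49% power at 0.5 SD.

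**2. Type 2 women who must be on diet alone.** The required fraction is 0.46/(1 − p).

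**3. Cost of adjusting for type, if 46/54 holds.** With no type 1 woman in the diet-only group, the squared correlation between diet-only status and type is φ² = 0.46p/[0.54(1 − p)]. The information left on medication after adjustment is 1 − φ². The unadjusted noncentrality is 0.833 × √(29 × 34/63) = 3.29, and adjustment multiplies it by √(1 − φ²), with 60 degrees of freedom.

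| Type 1 share p | Type 2 on diet alone | 1 − φ² | Adjusted power at 0.83 SD |
|---|---|---|---|
| 10% | 0.46/0.90 = 51% | 0.905 | 0.87 |
| 20% | 0.46/0.80 = 58% | 0.787 | 0.82 |
| 30% | 0.46/0.70 = 66% | 0.635 | 0.73 |
| 40% | 0.46/0.60 = 77% | 0.432 | 0.57 |
| 50% | 0.46/0.50 = 92% | 0.148 | 0.24 |
| 54% | 0.46/0.46 = 100% | 0 | not estimable |

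Above 54% the split cannot occur. The loss arises because few medicated type 2 women remain. They make up 0.54 − p of the sample: 0.24 × 63 ≈ 15 women at p = 30%, 0.14 × 63 ≈ 9 at 40%, and 0.04 × 63 ≈ 2.5 at 50%, against 29 on diet alone.

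**4. If fewer women are on diet alone.** Unadjusted power with 63 women at the same 0.83 SD:

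| Diet-only share | Group sizes | Power |
|---|---|---|
| 46% | 29 vs 34 | 0.90 |
| 30% | 19 vs 44 | 0.85 |
| 20% | 13 vs 50 | 0.75 |
| 10% | 6 vs 57 | 0.48 |

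**5. The two power claims together.** At a type 1 share of 10%, the split asks for only 51% of type 2 women on diet alone. The comparison by diabetes type is then 6 vs 57, where 90% power needs a difference of 1.41 SD, against 0.83 SD at 29 vs 34. A larger type 1 group helps the comparison by type but pushes the diet-only requirement towards 92% at p = 50%. The inputs that make one claim easier make the other harder.

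**The case against.** The other side has a fair case.

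- **No number is refuted.** A reader might infer that adequate power is absent. The protocol does not support that: with no effect size or SD stated, the claim can be neither reproduced nor disproved, and the 0.83 SD benchmark is not the protocol's. This stands; the claim is unsupported, not shown false.
- **A low type 1 share is not excluded.** A reader might infer that the 46/54 split must describe some other population. It need not: at a type 1 share of 10%, about half of the type 2 women on diet alone would suffice, and the abstract expects some women without medication. This stands too. But a low share weakens the claimed power by type.
- **Medication and type can be separated.** A reader might call the two aliased. While some type 2 women are medicated, type 2 appears in both groups and adjustment is possible. The confounding is partial, and complete only at a type 1 share of 54%.
- **No pooled test is specified.** The statistical section sets out no diet versus medication model, its covariates are given as examples, and model details may lie in documents not shown. The protocol already calls all secondary analyses exploratory. This limits severity. It does not rescue the power claim, whose premise and conclusion both stand in the article.
- **The primary comparison is within woman.** Each woman takes both meals, so type and stable medication status are largely balanced there. This stands in full.

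**Conclusion.** The statement of adequate power for diet versus diet+medication is unsupported. The size of the problem depends on a type 1 share that the protocol does not give. It is modest at 10–20% (51–58% of type 2 women on diet alone; adjusted power 0.87–0.82) and serious at 30–50% (66–92%; adjusted power 0.73–0.24). Partial confounding with diabetes type is present whatever share of type 1 women is enrolled. These results rest on type 1 women all using insulin, a two-sided 5% test and the illustrative 0.83 SD. Severity is low: the sample sizes of 63 and 76 and the primary analysis do not depend on the split.

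**What to change.** Either withdraw the adequate-power sentence for diet versus diet+medication, or restate it with four items: the source population of the 46%/54% figures, the expected type 1 to type 2 mix, the expected diet-only share among type 2 women, and the difference detectable with the resulting group sizes. The restated mix should also be the one used for the claim of power by diabetes type.

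Make any diet versus diet+medication comparison within type 2 women, or adjust it for diabetes type, and label it exploratory.

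The cost is about one sentence in the sample-size section and one line in the analysis section. The stated power will probably look less favourable. Recruitment, randomisation and the primary test need no change.

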### Study participation inclusion and exclusion criteria

All pregnant women over the age of 18 years, with pre-existing T1DM or T2DM, in their first trimester and a singleton pregnancy, will be considered for the study. Women who develop diabetes in pregnancy (i.e., gestational diabetes) will not be eligible for the study because they would not be offered CGM until 26–28 weeks’ gestation. Exclusion criteria include: (1) inability to understand English sufficiently to read the participant information sheet and provide consent (online supplemental materials A–C); (2) mental and/or psychological disorders that undermine informed consent; (3) cancer, digestive tract disorders; (4) lack of internet access on a computer or tablet at home. Detailed exclusion criteria are shown in table 1 (study screening questionnaires are provided in online supplemental materials D and E).

10.1136/bmjopen-2022-065388.supp1Supplementary data

**Table 1 T1:** Study participant inclusion and exclusion criteria

Inclusion criteria	Exclusion criteria
Women aged 18–45 years	Women under 18 or above 45 years of age
Singleton pregnancy	Multiple pregnancy
Women in the first trimester of pregnancy	Fetal congenital abnormality
Previously diagnosed with type 1 or type 2 diabetes mellitus	No diagnosis of diabetes
	Diagnosis of gestational diabetes
	Significant coexistent medical condition (e.g., overt diabetes complications, cancer, gut mobility or digestion disorder)
	Significant psychological (e.g., anorexia, bulimia) and/or mental disorders which undermine informed consent
	Dietary allergies or intolerance for the experimental meals
	Lack of internet access on a computer or tablet at home
	Unable to understand written English and provide informed consent

### Data collection stages and procedures

The study will proceed in three stages at the St James’s Hospital (LTHT) with the dietary intervention and interviews conducted remotely (e.g., participant’s home) (figure 1). All pregnant women with pre-existing T1DM or T2DM are scheduled for regular NHS clinical visits every 2 weeks throughout the pregnancy. Each woman has an assigned diabetes midwife who caseloads her pregnancy and liaises with the rest of the clinical care team. Due to COVID-19 and intermittent lockdowns, pregnant women only attend face-to-face meetings at the clinic when due for a scan (*a dating scan* at 10–12 weeks, an *anomaly scan* at 18–20 weeks and *growth scans* at 26–28, 32–34 and 36 weeks of pregnancy) unless deviated due to complications or early delivery. All women with T1DM and T2DM are currently offered CGM as part of their clinical care. The CGM data are automatically uploaded to a secure, remote clinical database, where it can be securely accessed and downloaded by the clinical team and authorised researchers.

**Figure 1 F1:**
[figure not shown]
Study flow chart. Participant will be monitored and in contact with the clinical and research team through the study, starting at 10–12 weeks’ gestation. At each clinical visit, routine data will be collected from each participant as standard of care (e.g., anthropometrics, blood samples and CGM). This information will be supplemented with lifestyle information (e.g., diet and sleep) collected directly from the participant via electronic and internet questionnaires. The maternal and offspring data available for analysis at each time point are listed below the timeline. The interventions will be delivered at two time points (18–20 and 34–36 weeks). CGM, continuous glucose monitoring; NHS, National Health Service.

The study will require patient consent (1) permitting secure access to routinely collected clinical details regarding maternal and offspring health at each clinical visit and delivery (i.e., height, weight, blood pressure, HbA1c, lipids), CGM data and delivery outcomes with approved study researchers; (2) permitting researchers to use the residual urine from routine clinically collected samples for metabolite analysis; (3) to conduct online and interview questionnaires to assess diet and lifestyle during each trimester at ~10–12, ~18–20, and ~28–34 weeks; and (4) a 10 mL blood sample to be taken with routine clinical bloods at visits ~10–12, ~18–20, and ~28–34 weeks for subsequent metabolomic and genetic analysis. Each participant will be contacted three times for a phone or video chat (participant preference) for ≤30 min each within 2 weeks of each clinical appointment.

#### Patient and public involvement

Patients or the public have not been involved in the design of this pilot and feasibility study. However, upon completion of the study, participants will be invited to provide insight and comments regarding the study itself, the burden enrolment and intervention, and identifying other research priorities relevant to the health condition that the researchers can integrate into future studies. They will also be asked if they consent to follow-up discussions and are keen to be updated on study results and publication material. These points will be invaluable for guiding future work in this area:

*First call between 10 and 12 weeks of pregnancy:* a member of the research team will provide details of the study with the participant and answer any questions. The participants will be instructed to record their dietary intake for 3 days, including 2 weekdays and 1 weekend, using the myFood24 app. The myFood24 is a validated online food diary system created to analyse nutritional intake, which has previously been used in pregnancies complicated by diabetes.^18^ Details on the participant’s recent physical activity levels (Par-Q for pregnancy)^19^ and sleep quality (Leeds Sleep Evaluation)^20^ will be recorded by interview (online supplemental materials F and G), while patterns and habitual mealtimes will be collected by myFood24.^21^ The dietary meal intervention in the study will also be discussed.

*Second call between 18 and 20 weeks of pregnancy:* participants’ compliance in the study and details on physical activity, sleep and habitual mealtimes will be re-recorded. A reminder and summary of when and how to use the myFood24 app will be given. The participant will also be instructed about how and when their study intervention’s first set of experimental meals should be consumed.

*Third call between 28 and 34 weeks of pregnancy:* participants’ compliance and information transfer as in the second call will be repeated. The participant will also be instructed about how and when their study intervention’s second set of experimental meals should be consumed. Subsequently, the participant will be thanked for their participation in the study and not contacted again after this point.

### Nested cross-over dietary meal intervention within the study

Shortly after their clinical visit at ~18–20 weeks and ~28–34 weeks, participants will be asked to consume standardised breakfast meal replacements in their own home, at breakfast time for 4 days. These will be two different experimental meals (A and B; matched for 400 kcal and 13 g of fat) consumed under free-living conditions. The experimental meals will appear and taste similar but differ in protein quantity which will alter how quickly the glucose in each meal is absorbed into the blood.^22^ One experimental meal will have 20 g of vegan and gluten-free protein powder added, which slows gastric emptying and glucose absorption into the blood to a rate that is comparable with commonly consumed whole-grain breakfast cereals (eg, steel-cut or rolled oats; GI ≈40). The other experimental meal will have no added protein. The experimental meals (labelled A or B) with a drink shaker are stored in a box by the research team in a COVID-19-safe laboratory. Each participant will be assigned to one of six random orders to consume the experimental breakfast meals (AABB, ABAB, BBAA, BABA, ABBA, BAAB) over 4 days using an online randomiser (https://www.random.org/integer-sets/). This will be done by block randomisation to assign 12–13 participants to each of the six possible orders of meal consumption, which the participant will follow for both sets of meals (i.e., ~18–20 and ~28–34 weeks). The participant will only need to pour the powder into the shaker, add cold water to the line marked on the cup (500 mL), and consume within 5 min.

The powder is a nutritionally complete meal replacement in drink form; every meal contains a balance of protein, carbohydrates, essential fats, fibre, plus all 26 essential vitamins and minerals, and phytonutrients. Additionally, the product is low in sugar, lactose-free, contains no nuts or palm oil, and has a long shelf life. The powder is commercially available and is produced in facilities that meet highest quality standards. This product was chosen to minimise time burden for participants and it is free from many commonly avoided food items (i.e., lactose, nuts, gluten and meat).

Participants will be asked to avoid consuming other foods and drinks (aside from water) for 2 hours, after which they may consume food as usual. However, they are freely permitted to measure their own blood glucose levels at any point and will be advised to manage any hyperglycaemic or hypoglycaemic events, even if this means eating or drinking within 2 hours of the meal. Participants will be asked to inform the research team of any events by email as soon as possible.

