### Statistical analysis considerations

All standard CGM metrics will be calculated, with AUC glucose as the primary CGM metric (mean±SD). The primary analysis will be the effect of dietary protein on AUC glucose for the 24-hour window immediately after each study meal. The analysis will be constructed as pairwise linear model with study meal (0=low protein, 1=high protein) regressed against 24-hour mean AUC glucose and adjusted for study parameters (e.g., randomised meal order) and participant covariates (e.g., maternal age, ethnicity, parity, BMI, gestational age, physical activity and sleep quality). Statistical significance will be set at p<0.05, where a p<0.05 for study meal will suggest a significant effect of dietary protein on 24-hour postprandial AUC glucose. The direction and significance of covariates will be investigated to identify study and participant mediators of the association. Statistical analysis will be conducted in R studio and SPSS (Ver. 29+).

Secondary research objectives include (1) the association between dysglycaemia and maternal and newborn health, and (2) the association between maternal diet in early pregnancy with dysglycaemia during pregnancy. These analyses will also be performed using regression models adjusted for covariates, with the assessment of early diet on longitudinal changes in dysglycaemia also adjusted for time points of AUC (i.e., mixed-model). The association between early maternal diet and AUC will be performed using three distinct dietary metrics (calculated from myFood24):

1. Overall diet quality

The association between diet quality and dysglycaemia will be assessed using an overall diet quality score.^24^ This scoring method has been modified and used previously to assess maternal diet quality in a multiethnic prospective birth cohort.^25^ The modified Alternative Healthy Eating Index (mAHEI) score is calculated using the following method; an individual will receive 10 points for each of the following food categories when they consume above or below a threshold of: ≥5 servings of vegetables, ≥4 servings of fruits, ≥1 serving of nuts or soy proteins, ≥3 servings of whole grains, a ratio of ≥4 servings of fish to 1 serving of meat and eggs, and ≤0.5 servings of less-healthy foods (i.e., fried foods and processed meats). Intermediate intake is scored proportionally between 0 and 10. The maximum mAHEI score is 60; the higher the score, the more healthful the participant’s diet.

2. Macronutrient

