## Discussion

The INFORMED clinical trial is double-blinded cross-over randomised clinical trial to evaluate the effect of dietary protein within experimental meals on dysglycaemia in women with pre-existing type 1 or type 2 diabetes. Additionally, we will explore (1) the association between dysglycaemia and maternal and newborn health, and (2) the association between maternal metabolic profiles in early pregnancy with dysglycaemia in later pregnancy, which may provide insights into novel precision therapies for women with DIP.^26^ The identification of dietary mediators of glucose variability will aid in the development of more efficacious and appropriate strategies to control glucose levels and minimise maternal and offspring risks in women with DIP.^12 13 26^

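### The meals are matched for energy and fat, so the test of study meal measures more protein together with less carbohydrate, not dietary protein alone

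*Protocol article*

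**What the plan says.** In the protocol article, the section on the nested cross-over meal intervention describes "two different experimental meals (A and B; matched for 400 kcal and 13 g of fat) consumed under free-living conditions". One meal receives 20 g of a vegan, gluten-free protein powder. For the comparator, "The other experimental meal will have no added protein". The meals are said to "differ in protein quantity which will alter how quickly the glucose in each meal is absorbed into the blood", so the stated mechanism is the speed of absorption. The section does not say that the amount of carbohydrate differs.

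Under Statistical analysis considerations, the primary model regresses 24-hour AUC glucose on a 0/1 indicator for study meal, adjusted for meal order and participant covariates. The decision rule follows: "where a p<0.05 for study meal will suggest a significant effect of dietary protein on 24-hour postprandial AUC glucose". The Discussion describes the trial as one "to evaluate the effect of dietary protein within experimental meals on dysglycaemia". The Abstract is more neutral: "The primary outcome is the effect of experimental meals (high vs low protein) on postprandial glycaemia".

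**The concern.** The energy and fat match is a legitimate design. The difficulty lies in the conclusion attached to it. If two meals have the same energy and the same fat, and one has more protein, something else that carries energy must be lower in that meal. Here that can only be carbohydrate, counting fibre as part of it. The meal indicator therefore stands for two changes at once, and the decision rule credits one of them.

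This matters because less carbohydrate at breakfast would be expected to lower glucose AUC with no contribution from protein, which is the direction the trial hopes to see. A significant result could be partly or wholly due to the smaller carbohydrate load and would still be reported as a protein effect. A clinician might then advise adding protein to a usual breakfast, when the trial had tested replacing carbohydrate with protein.

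**Working it through.** **Inputs from the article (meal intervention section):** 400 kcal and 13 g fat in both meals; 20 g protein powder in one meal and none added in the other; the meals contain protein, carbohydrate, fat and fibre.

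**Assumptions (not in the article):** energy factors of 9 kcal/g for fat, 4 for protein, 4 for available carbohydrate and about 2 for fibre; powder that is 60–100% protein; where needed, 10–20 g of protein in the base meal.

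**1. Energy left after fat.** 13 × 9 = 117 kcal, and 400 − 117 = 283 kcal in each meal. Ignoring fibre, that is 283 / 4 = 70.75 g of protein plus carbohydrate.

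**2. The constraint.** With energy and fat equal, 4 × (change in protein) + 4 × (change in carbohydrate) = 0. Each net gram of protein gained is a gram of carbohydrate lost. This needs no assumption about powder purity or base protein.

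**3. Size if the powder replaces carbohydrate gram for gram.** The powder supplies 20 × 0.6 = 12 g to 20 × 1.0 = 20 g of protein, so the carbohydrate gap is 12–20 g. The low-protein meal holds at most 70.75 g of carbohydrate, so the relative loss is at least 12 / 70.75 = 17.0% to 20 / 70.75 = 28.3%.

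**4. Size if base powder is cut to make room.** Keep fat at 13 g and count the powder as 20 × 4 = 80 kcal. The non-fat base then scales by (283 − 80) / 283 = 0.717 and loses 28.3% of its own protein. The net protein gain, and so the carbohydrate gap, is (20 × purity) − 0.283 × (base protein):
- purity 0.6, base protein 20 g: 12 − 5.65 = 6.3 g
- purity 1.0, base protein 10 g: 20 − 2.83 = 17.2 g

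Steps 3 and 4 together give a range of roughly 6–20 g.

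**5. Could fibre absorb the difference?** Offsetting 48–80 kcal through fibre alone would take 48 / 2 = 24 g to 80 / 2 = 40 g less fibre. That is implausible in a 400 kcal drink and would still be a carbohydrate difference. Fibre could take part of the trade, so the gaps in available carbohydrate above are approximate.

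**6. Could the powder sit on top of an identical 400 kcal base?** Its protein alone adds 12 × 4 = 48 to 20 × 4 = 80 kcal, giving 448–480 kcal, or 12–20% above the stated 400. That contradicts the match. The contrast would then be added protein plus added energy, which is still not protein alone.

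**7. Could the model separate the two?** No. Each meal has one fixed composition, so its carbohydrate content is fully determined by the 0/1 meal indicator. No covariate can separate them. The planned macronutrient regressions are exploratory analyses of recorded diet and do not alter the meal contrast.

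**The case against.** The strongest reply is that this is a matter of wording. In any energy-matched comparison, raising one macronutrient lowers another, and an effect of protein is common shorthand for that substitution. The match is stated openly, so a careful reader can work out the trade. The Abstract already frames the result as an effect of meals, the Introduction speaks of meal replacements together with protein, and the decision rule says only that significance will suggest an effect.

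Much of this stands: the estimate, test and design are unaffected. But the shorthand appears beside an account that names only protein quantity and absorption speed, so nothing tells the reader that the glucose load also changes. The rule governs the primary conclusion, and its hedged verb still names protein as the cause.

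A second reply is that the recipe is not shown. That also stands as far as the size of the gap goes. It affects the remedy too, since substitution wording would be wrong if the powder is added on top of a 400 kcal base. It does not rescue the rule, because the protein-only attribution fails on either reading.

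Three stronger readings are not supported:
- A reader might infer that the comparison is biased or invalid. It is not: the randomised contrast between the two meals is sound.
- A reader might count the missing grams as an error. A condensed article may leave composition to the full protocol.
- A reader might take the sample size section's mention of "the effect of diet composition and glycaemic load on metrics of CGM" to declare glycaemic load a trial exposure. That sentence only describes a gap in existing evidence.

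**Conclusion.** The point holds as a misattribution in the primary decision rule, repeated in the Discussion's aim. If the finished meals are matched as stated, the trial estimates the joint effect of more protein and less carbohydrate at equal energy and fat. That a carbohydrate gap exists follows from the stated match and standard energy factors. Its size, roughly 6–20 g, rests on assumed powder purity (60–100%), assumed base protein (10–20 g where base powder is cut), the way the energy was balanced, and ignoring fibre.

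It would go too far to conclude that carbohydrate explains any effect found. The article gives no basis for converting this gap into a change in 24-hour AUC, so no effect on the outcome is quantified. What changes is what a significant result may be said to show.

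**What to change.** 1. Confirm from the recipe that the finished meals, powder included, each contain 400 kcal and 13 g fat.
2. If they do, reword the decision rule under Statistical analysis considerations so that p<0.05 for study meal suggests an effect on 24-hour AUC glucose of replacing carbohydrate with protein at equal energy and fat. Word the aim in the Discussion in the same way.
3. Report the grams of protein and available carbohydrate in A and B alongside the result.
4. If the powder is instead added on top of a 400 kcal base, correct the matching statement and describe the contrast as added protein plus added energy.

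The cost is one check of the recipe, two changes of wording and one line of composition. Meals, randomisation, sample size, model and test are unchanged. The downside is that the trial gives up any claim to a protein effect separate from carbohydrate load.
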